### Sample size calculations

Considering the minimum detectable change of 1.0 cm or 100 mm reported for LMM CSA [50], the sample size was estimated a priori to detect a minimum difference of 1.0 point  in LMM CSA between LSER and LSE, or 2.0 points between LSER and minimal intervention, assuming a common standard deviation (*SD*) of 2.5 points based on our pilot study [29], a medium effect size of 0.32, an alpha of 0.05, statistical power of 85%, and a correlation of 0.5 among repeated measures,  for between–within repeated measures analysis of variance (ANOVA). The calculations revealed that a sample size of 75 is required. However, while anticipating a 20% dropout rate (*n* = 15), a total sample size of 90 (30 per group) will be finally required. The sample size was calculated using G Power 3.1.9.2 software [51].

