**Discussion:**

To our knowledge, this study will be the first powered randomized controlled trial to compare the effectiveness of LSE training with and without RUSI biofeedback in individuals with NCLBP. The outcome of the study may provide evidence for the effectiveness of LSE with RUSI biofeedback on enhancing the recovery of the lumbar multifidus muscle in individuals with NCLBP.

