According to the latest systematic review [32] to summarize the evidence regarding the effectiveness of LSE on LMM morphology, very low- to low-quality evidence exists that LSE improves LMM CSA post-intervention or compared to medication, general exercise, or general physiotherapy in patients with non-specific LBP. However, only one RCT [28] (conducted among acute LBP patients) of the five included RCTs [28, 33–36] used RUSI as biofeedback. Furthermore, on the basis of two small trials [28, 37] in which one included patients with acute LBP [28] and the other included patients with  chronic LBP [37], the review [32] found no evidence to support the correlation between changes in LMM CSA  and changes in pain or disability. Thus, it is imperative to explore  if the addition of RUSI biofeedback in LSE training would provide more favorable effect on LMM CSA compared to LSE training without RUSI biofeedback, and to examine the correlation between changes in LMM CSA and LBP or LBP-related disability among individuals with NCLBP. 

Our recent pilot study [29], even though was limited to being a single-group pretest-posttest design, suggests the feasibility of conducting a large-scale RCT  to determine the efficacy of LSE with RUSI biofeedback in individuals with NCLBP. The use of LSE with RUSI biofeedback resulted in significant improvement in LMM CSA by 1.7 points, pain by 3.9 points, and  disability by  4.5 points. However, no significant improvement in  physical and mental health was observed after the intervention, which could be attributed to the shorter treatment (12 sessions) provided [29]. Thus, the purpose of this study is to determine the effectiveness of LSE with RUSI biofeedback in individuals with NCLBP. The primary outcome will be LMM CSA whereas the secondary outcomes include  pain, functional disability, and QOL. 

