## Methods/Design

### Hypothesis 

We hypothesized that patients receiving LSE with RUSI biofeedback will demonstrate significant improvement in LMM CSA, pain, functional disability, and QOL compared to those receiving LSE without RUSI biofeedback or minimal intervention (control). 

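### The stated 85% power does not apply to a 1.0-point difference between LSER and LSE: on the protocol's own inputs that contrast has about 28% power at one visit, and at most about 58% on the most favourable reading.

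*Protocol article*

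**What the plan says.** In the protocol article, the section Sample size calculations states that "the sample size was estimated a priori to detect a minimum difference of 1.0 point" in multifidus cross-sectional area between LSER and LSE, or "2.0 points between LSER and minimal intervention". It assumes a common SD "of 2.5 points based on our pilot study", "a medium effect size of 0.32", alpha 0.05, "statistical power of 85%, and a correlation of 0.5 among repeated measures", for a between–within repeated measures ANOVA. The result is 75, raised by 15 for a 20% dropout to 90, or 30 per group. The section does not say whether the group effect, the time effect or the interaction was powered.

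The Hypothesis section sets LSER against both comparators: "compared to those receiving LSE without RUSI biofeedback or minimal intervention (control"). The Discussion paragraph of the Abstract goes further for one of them: "this study will be the first powered randomized controlled trial to compare the effectiveness of LSE training with and without RUSI biofeedback". Outcome assessment fixes three visits: baseline, 8 weeks and 3 months. The statistical analyses section plans a mixed between–within ANOVA followed by post hoc tests. It does not plan a baseline-adjusted ANCOVA.

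**The concern.** A sample size for a three-group omnibus F test is not a sample size for one pair of groups, least of all the pair with the smaller difference. When the three arm means are spaced 0, 1 and 2, the 2.0-point gap between the extremes supplies most of the omnibus signal. The sample size section nevertheless names the 1.0-point pair as what the trial can detect, and the Abstract calls the trial powered for that comparison.

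A group main effect in a repeated-measures ANOVA also averages over every visit. One of the three visits here is baseline, where randomization makes the expected arm means equal.

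What is at stake is how an LSER versus LSE result is read. If a trial labelled powered returns a non-significant difference, readers may take it as evidence that biofeedback adds nothing, although the design would often miss the stated difference.

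**Working it through.** **Inputs.** From Sample size calculations: differences 1.0 and 2.0, SD 2.5, f = 0.32, alpha 0.05, power 85%, correlation ρ = 0.5, N = 75. From Outcome assessment: m = 3 visits. From the randomization section: three groups, 1:1:1. Two-sided testing of pairs is my assumption, since sidedness is not stated.

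**Step 1. Reproduce the plan's figure.** For the between-groups effect in a repeated-measures ANOVA, λ = N·f²·m / [1 + (m − 1)ρ], with 2 and N − 3 degrees of freedom.
- N = 75: λ = 75 × 0.1024 × 3 / 2 = 11.52, power 0.854.
- N = 74: power 0.849.

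So 75 is the exact threshold. Other options miss it: the interaction needs 27, the within-subject effect 21, one-way ANOVA 111, two measurements 84, and four measurements 70 (72 in equal groups).

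**Step 2. Where f comes from.** Arm means 0, 1 and 2 have a standard deviation of √(2/3) = 0.816, and 0.816 / 2.5 = 0.327, close to the stated 0.32. The two differences in the text thus appear to have been combined into a single omnibus effect.

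**Step 3. Power for LSER versus LSE = 1.0.** Noncentral t, noncentrality = difference / (SD·√(2/n)), 2n − 2 degrees of freedom.

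The SD for each analysis is:
- One visit: 2.5. Change from baseline has the same SD, because 2.5·√(2(1 − 0.5)) = 2.5.
- One visit, baseline-adjusted: 2.5·√(1 − 0.5²) = 2.165.
- Mean of both follow-ups, baseline-adjusted: 2.5·√0.5 = 1.768.

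| Analysis | 24 per arm | 25 per arm | 30 per arm |
|---|---|---|---|
| One visit or change | 27% | 28% | 33% |
| One visit, baseline-adjusted | 35% | 36% | 42% |
| Mean of both follow-ups, baseline-adjusted | 48% | 50% | 58% |

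Worked example at 25 per arm, one visit: 2.5 × √(2/25) = 0.707, noncentrality 1 / 0.707 = 1.41, power 28%.

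If the 1.0 point is granted in the average of all three visits (SD 2.5·√(2/3) = 2.041), power at 25 per arm is 40%. If baseline is equal, that average difference is 2/3 of a point and power is 20%. A Bonferroni correction for three post hoc pairs, used as an illustration because the article names no correction, lowers the two single-visit figures at 25 per arm to 15% and 21%.

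**Step 4. What 85% power would detect.** At 25 per arm, about 2.2 points at one visit, or about 1.9 points if baseline-adjusted. At 24 per arm the rounded values are the same.

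**Step 5. The omnibus tests with equal baselines.** If arms differ by 0, 1 and 2 only at the two later visits, the visit-averaged means are 0, 2/3 and 4/3, and f = 0.327 × 2/3 = 0.218.
- Group effect: λ = 75 × 0.218² × 1.5 = 5.33, power 51% (60% at N = 90).
- Interaction: the squared interaction terms sum to 1.333, so λ = 25 × 1.333 / (2.5² × 0.5) = 10.67, power 73% (82% at N = 90).

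**Step 6. LSER versus control = 2.0.** At 25 per arm: 79% at one visit, 89% baseline-adjusted. At 30 per arm: 86% and 94%.

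**Step 7. Evaluable number.** A 20% loss from 90 leaves 90 × 0.8 = 72, or 24 per arm, not 25. Keeping 75 would require 75 / 0.8 = 93.75, that is 94.

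**The case against.** The best defence is that the article ties its power to an ANOVA, and that 1.0 and 2.0 merely generated the effect size. On that reading the software step is correct, and 75 is the right answer to the question put to it. This stands as far as it goes: the error lies in what the 85% is said to detect, not in the software output. The powered effect is also inferred from the exact match, and should be described as such.

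Three stronger readings are tempting, and the documents do not support them.
- A reader might infer that the trial is underpowered throughout. The hypothesis names two comparators, and LSER versus control at 2.0 points comes near or above 85% in most readings. The interaction test at the full 90 reaches 82%, a modest shortfall.
- A reader might infer that the 2.0-point gap is an error, because in the pilot the intervention "resulted in significant improvement in LMM CSA by 1.7 points", less than 2.0. The pilot gave 12 sessions, whereas this trial gives 16 (twice weekly for 8 weeks), so a larger assumed effect is debatable but not a contradiction. Power at 1.7 points is a scenario only.
- A reader might infer that any non-significant LSER versus LSE result is inconclusive. At 25 per arm the 95% interval has a half-width of about 1.2 to 1.4 points, so an observed difference of −0.6 would exclude a 1.0-point benefit.

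It is also fair that the Dissemination section already commits to publishing inconclusive results, so misreading is a risk and not a certainty.

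**Conclusion.** The power statement is wrong as written. Eighty-five per cent with 75 participants is not power for a 1.0-point difference between LSER and LSE. For that pair, power is about 28% to 50% at 25 per arm and 33% to 58% if nobody is lost, depending on the analysis; correction for multiple pairs lowers it further. The statement that the design misses the target about two times in three or more belongs to the single-visit analyses at 25 per arm only. The omnibus claim also falls short once baseline means are taken as equal.

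These results rest on the article's own SD and correlation, two-sided alpha of 0.05, equal arms and, for the omnibus figures, arm differences that are the same at both follow-ups. None of the readings tried brings the 1.0-point pair near 85%. That the between-groups option was used is inferred, but the pairwise figures do not depend on it.

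**What to change.** Wording only:
1. Delete the claim of 85% power for 1.0 point between LSER and LSE.
2. State power for each contrast under the analysis actually planned. At 25 per arm this is about 28% for LSER versus LSE at 1.0 point, with 85% power only for about 2.2 points, and about 79% for LSER versus control at 2.0. Give baseline-adjusted figures (36%, about 1.9 points, and 89%) only if the plan adopts a baseline-adjusted ANCOVA.
3. Base the final numbers on 24 evaluable per arm, as a 20% loss from 90 implies. The LSER versus LSE figures then become about 27%, or 35% if baseline-adjusted; LSER versus control becomes 77%, or 88%.
4. Limit the claim in the Abstract and Discussion that this is a powered trial of LSE with versus without biofeedback.
5. Report the LSER versus LSE difference with its 95% confidence interval, and call a non-significant result inconclusive when that interval still includes a 1.0-point benefit.

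The cost is a less favourable stated power. No extra patients are needed, and follow-up was in any case expected to be complete by September 30, 2021.

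### The 20% dropout allowance is taken on the wrong base: 90 randomised with 20% lost leaves 72, not the required 75

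*Protocol article*

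**What the plan says.** The section Sample size calculations of the protocol article gives the inputs as "a medium effect size of 0.32", "a correlation of 0.5 among repeated measures" and "an alpha of 0.05, statistical power of 85" per cent, for a between–within repeated measures ANOVA. It reports the result before dropout: "The calculations revealed that a sample size of 75 is required". It then says that, "anticipating a 20% dropout rate", which it equates with 15 people, "a total sample size of 90 (30 per group) will be finally required". The section on randomisation and blinding fixes the same number for conduct: envelopes numbered 1 to 90, allocated 1:1:1, 30 per group.

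**The concern.** The 15 shows how 90 was reached: 20% of 75, added to 75. A dropout rate is a share of the people enrolled, and 90 are enrolled. Applied to 90, the stated rate removes 18 people, not 15. The three stated figures (75 required, 20% dropout, 90 randomised) therefore cannot all hold.

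At stake is whether the trial keeps the number its own calculation asks for under its own dropout assumption. A reader will take the trial as protected against 20% loss at 85% power. The article also presents itself as a powered trial and criticises earlier trials for lacking an a priori power calculation, so the figure is one that readers will rely on.

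**Working it through.** **Inputs.** From Sample size calculations: f = 0.32, alpha 0.05, power 85%, correlation ρ = 0.5, 75 required, 20% dropout taken as 15, final total 90. From Outcome assessment: m = 3 measurements (baseline, 8 weeks, 3 months). From the randomisation section: 3 groups, 1:1:1.

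**Step 1: reproduce the 75.** The article does not say which effect in the ANOVA was powered. The between-group main effect reproduces its figure. Its noncentrality is λ = f² × N × m / (1 + (m − 1)ρ), with 2 and N − 3 degrees of freedom. With m = 3 and ρ = 0.5 this is λ = 0.1024 × N × 3/2 = 0.1536 × N.

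| N | λ | Power |
|---|---|---|
| 72 | 11.06 | 83.8% |
| 74 | 11.37 | 84.9% |
| 75 | 11.52 | 85.4% |
| 90 | 13.82 | 91.6% |

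So 75 is the smallest N that reaches 85%. The published figure is reproduced, and it has no slack.

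**Step 2: reproduce the 90.** 0.20 × 75 = 15, and 75 + 15 = 90, which is 75 × 1.20.

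**Step 3: apply the stated dropout to those randomised.**
- Lost: 0.20 × 90 = 18.
- Remaining: 90 − 18 = 72, or 24 per arm against the 25 required.
- Shortfall: 75 − 72 = 3.
- Dropout that 90 covers while retaining 75: 15/90 = 16.7%.

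**Step 4: the inflation that matches 20%.** 75/(1 − 0.20) = 93.75, so 94 in total. With equal arms, 25/0.80 = 31.25, so 32 per arm and 96 in total.

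**Step 5: effect on power.** On the plan's own inputs, 72 gives 83.8%. That is 1.2 percentage points below the stated 85% and 1.6 below the 85.4% at 75.

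**Step 6: sensitivity to rounding of f.** The section also gives differences of 1.0 and 2.0 points, "assuming a common standard deviation (*SD*) of 2.5 points". If the arm means are spaced 0, 1, 2 (an assumption for the gap between LSE and control), f = √(2/3)/2.5 = 0.327. Then f² = 0.1067, and at N = 72 λ = 0.1067 × 72 × 1.5 = 11.52, with power 85.4% (85.35% before rounding). On that value the smallest sufficient N with equal arms would have been 72.

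**The case against.** The arithmetic is not open to dispute. The case on the other side is about consequence.

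- **Rounding.** The shortfall in power appears with f = 0.32 and disappears with 0.327 (Step 6). This is true and should be said. But the plan states 0.32 and gets its 75 from it. With 0.327 the requirement would have been 72, which is not what the plan reports.
- **Dropouts may still contribute.** The section on data processing and statistical analyses includes every randomised participant who has any outcome data, whether or not they were followed up. Someone who misses only the 3-month visit need not be wholly lost, so 72 and 83.8% are closer to a worst case. That stands as a qualification. It does not repair the allowance, because the sample size section itself treats dropouts as lost. The analysis named is a mixed ANOVA, and the article gives no way of handling missing follow-up values that would let dropouts count in full.
- **The test is inferred.** If the group-by-time interaction had been powered with the same inputs, only 27 would be needed, and three people would not matter. But that option does not give 75. The between-group test does.
- **Common shortcut, small effect.** Adding 20% is often done, the dropout rate is itself a guess, and one person per arm is little. This argues for a light correction, not for leaving the figure as it is.

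**Conclusion.** The concern holds. The 20% was applied to the number needed for analysis instead of the number randomised. At the stated dropout, 90 randomised yields 72, 3 fewer than required, and 90 protects against 16.7% loss only.

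The head counts rest on nothing beyond the article's own numbers. The power figures (85.4% at 75, 83.8% at 72) rest on three conditions: the between-group F test over three measurements, f at its stated 0.32, and dropouts contributing no information. Relaxing the second or third brings power at 20% dropout to about 85%. The error is a wrong statement about a figure readers will rely on. It does not threaten the validity of the trial.

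**What to change.** Replace the dropout sentence in Sample size calculations with a statement to this effect:

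> Randomising 90 participants (30 per group) retains the required 75 if dropout is no more than 16.7%. At 20% dropout, 72 remain, and power on the stated basis (between-group test, f = 0.32) is about 84%.

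The authors may add that the unrounded effect size of 0.327 gives 85.4% at 72, provided they state the arm means behind it.

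The cost is one sentence and a slightly less favourable power figure. Raising the target to 94 (96 with equal arms) would have been the alternative at the design stage. The Trial status section puts first enrolment in August 2019 and expected completion of follow-up at 30 September 2021, so restating the allowance is the practical course. Nothing in the conduct or the analysis changes.

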### Data processing and statistical analyses

All data will be carefully recorded in a logbook and electronically using Microsoft Excel sheets. Data values will be double-checked for missing values and errors before transfer into SPSS for reporting and statistical analysis. Intention to treat (ITT) analysis will be applied with all randomized participants who have any outcome data available for analysis, included in the trial regardless of the presence or absence of follow-up. All statistical analyses will be conducted on IBM SPSS Statistics version 23.0 (IBM Co., Armonk, NY, USA) with a *P*-value < 0.05 to be considered significant for all tests.

A normality test for the dependent variables will be examined using the Kol mogorov–Smirnov and Shapiro–Wilk test. Descriptive analysis will be used to summarize the data with the use of mean (SD), frequencies, and percentages. One-way ANOVA (for normally distributed data) or Kruskal–Wallis (for skewed data) test will be used to compare baseline continuous variables whereas the chi-square test will be used to compare baseline categorical variables among the three groups. Mixed between–within subject ANOVA will be applied to evaluate time effect, group effect, and group by time interaction effect  in all outcomes if the data is normally distributed. Otherwise, Friedman’s ANOVA and Kruskal–Wallis test will be applied to evaluate within-group and between-group differences, respectively, when the data is skewed. Post hoc analysis will be applied for any significant within- or between-group differences detected. The effect size will be computed to evaluate the magnitude of change in all the outcomes. To examine the relationship between changes in LMM CSA and pain or disability, correlation and regression analyses will be performed for all the intervention groups.

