### Participants and recruitment

Patients with LBP attending outpatient physiotherapy and those referred for physiotherapy by orthopedists will be screened for their suitability to participate in the study. Participants’ eligibility will be ensured through history taking and physical examinations. The participants will be included if they (1) are male or female between the age of 18 and 60 years, (2) have a primary complaint of non-specific LBP with or without leg pain for 12 weeks or more, and (3) are able to read and understand Hausa or English language or both. Part icipants will be excluded if they (1) have a history of spine surgery; (2) have obvious deformities affecting the trunk or upper and lower extremities; (3) have serious spinal pathology such as infection, fracture, metastases, and cauda equine syndrome; (4) have a history of medical or surgical conditions that might hinder exercise performance; and (5) are pregnant or lactating women. Participants meeting the eligibility criteria and who accept willingly to participate will be given oral and written information about the study procedures. They will also be informed about their rights to withdraw from participation at any time without prejudice. Informed consent will be obtained via signature or thumbprint.  Participants’ baseline demographic and clinical variables, such as age, gender, marital status, education level, employment status, pain duration, height, weight, and body mass index will be collected and recorded after group allocation. The participants will be identified only by their initials using  research notes.

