### Rando mization and blinding

A record clerk who will not be involved in the assessment and treatment of participa nts will be responsible for the random allocation of participants into different intervention groups. The participants will be randomly assigned into LSE group, LSE with RUSI biofeedback (LSER) group,  or minimal in tervention (control) group in a 1:1:1 ratio (i.e., 30 participants per group) (Fig. 1). Consecu tively numbered (1 to  90) sealed opaque envelopes will be prepared using a computer-generated randomization sequence with permuted blocks of varying sizes (i.e., 3 and  6) by an independent statistician. Once a participant fulfilled the inclusion criteria and give consent for the study, the record clerk will perform the randomization by picking a sequential envelope and assign the participant to the group written in the envelope. All assessors will be blinded to participants’ group allocation. However, because of the nature of the interventions, it will be difficult to blind the participants and investigators (physiotherapists) to treatment allocation. Unbinding conditions will not occur but maybe only permissible when there is a medical emergency.

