#### Lumbar multifidus muscle cross-sectional area

The procedure for the LMM CSA will be identical to that described in previous studies [30, 38]. We found a within-day assessor intra-rater reliability during our pilot trial (*n* = 10) [29] to be excellent (intraclass correlation coefficients = 0.96) similar to findings of previous studies [39, 40]. Also, LMM CSA measurements obtained using RUSI have been validated by comparison with magnetic resonance imaging measurements [40]. The imaging of the LMM CSA will be measured at the L5 level using real-time ultrasound apparatus (Edan D3 version 1.6, China) with a 5-MHz curvilinear transducer. Participants will be placed on prone lying, on a plinth with arms by their sides and head turned to a preferred side. To keep the lumbar spine in a neutral position, a pillow will be placed under the hips to make the lower lumbar spine flat. The L5 spinous process will be identified by palpation, and the skin will be marked using a pen for reference. An acoustic coupling gel will be applied to the skin and the transducer head. Thereafter, the transducer head will be placed longitudinally along the midline of the lumbar spine to confirm the L5 level. The transducer head will be then placed transversely over the spinous process of L5 to obtain imaging of the spinous process and laminae along with the LMM on both sides of the spine. Transverse images of the LMM will be obtained bilaterally with the small side (thinner) being considered as the LMM CSA of the patient. Measurements will be taken during maximal voluntary isometric contraction. To ensure accuracy, average measures of three images of the LMM will be taken. The L5 level is chosen in this study because previous studies indicate that decreased LMM CSA and increased side-to-side asymmetry are common at this level [30, 41].

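### Baseline variables are significance-tested between randomised arms but none enters the outcome model as a covariate, which costs precision in the group main effect and in single-time-point contrasts

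*Protocol article*

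**What the plan says.** **Baseline tests.** Under Data processing and statistical analyses, one-way ANOVA (or Kruskal–Wallis if skewed) "will be used to compare baseline continuous variables whereas the chi-square test will be used to compare baseline categorical variables among the three groups". The same section sets P < 0.05 for all tests. It does not say what follows from a significant baseline result.

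**Outcome model.** A mixed between–within ANOVA "will be applied to evaluate time effect, group effect, and group by time interaction effect". No covariate is named. Baseline is one of the three measurement occasions (Outcome assessment), so it enters as a response level. The fallback for skewed data is Friedman and Kruskal–Wallis, neither of which takes a covariate. Regression is mentioned only for relating muscle area to pain or disability.

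**What is collected.** Under Participants and recruitment: "age, gender, marital status, education level, employment status, pain duration, height, weight, and body mass index will be collected and recorded after group allocation". Eligible patients "are male or female between the age of 18 and 60 years".

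**Allocation.** It uses a "computer-generated randomization sequence with permuted blocks of varying sizes", 30 per arm, with no stratification factor named.

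**Primary outcome.** "Transverse images of the LMM will be obtained bilaterally with the small side (thinner) being considered as the LMM CSA of the patient". This is an absolute area, not scaled to body size.

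**The concern.** Randomisation makes the null hypothesis of a baseline test true, so a small P value shows only that chance produced a difference. It says nothing about whether that variable predicts the outcome, which is what decides whether adjustment helps. With no stated consequence, a significant result leaves room for a covariate chosen after seeing the data, and a non-significant one for a false assurance of balance.

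Meanwhile the variables that could help are left out of the model. The outcome is an absolute muscle area in adults of both sexes over a wide age range. Each outcome's own baseline value, sex, height, weight and BMI are all recorded. What is at stake is precision in a trial of 25–30 per arm, most of all for the comparison of exercise with and without biofeedback, where the target is only 1.0 point.

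**Working it through.** **Inputs from the article.** SD 2.5, targets 1.0 and 2.0 points, f = 0.32, alpha 0.05, power 85%, correlation 0.5 among repeated measures, N = 75 raised to 90 (Sample size calculations); three occasions; nine baseline variables; five outcome scores (muscle area, NPRS, RMDQ, PCS-12, MCS-12). Points of muscle area are read as cm².

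**Assumptions (not in the article).** Men exceed women by D = 1.0 to 2.5 cm², and half the participants are male.

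**1. The article's own figure.** For the between-factors test in repeated-measures ANOVA, λ = N f² m / (1 + (m − 1)ρ) = 75 × 0.1024 × 3 / 2 = 11.52 on 2 and 72 df. Power is 0.854, and 75 is the smallest N that reaches 85%. The same test with two occasions needs 84, and the within–between interaction option with three occasions needs 25. Of the options tried, only the group main effect over three occasions reproduces N = 75.

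**2. False alarms.** Nine independent tests: 1 − 0.95⁹ = 0.37, with 9 × 0.05 = 0.45 expected. With the five baseline outcome scores: 1 − 0.95¹⁴ = 0.51, with 0.70 expected. Height, weight and BMI are correlated, so these are upper-end values.

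**3. Where stable variation sits.**
- *Group main effect.* The variance of a participant's mean is (1 + 2 × 0.5)/3 = 0.67 SD². A stable covariate explaining a share R² of the variance reduces this to 0.67 − R². At assumed R² of 0.1 to 0.4, power at N = 75 rises from 0.854 to 0.908–0.998.
- *Group-by-time interaction.* A participant's constant level cancels. In a simulation (4,000 trials per setting, 25 per arm, arm means equal at baseline and 0, 1, 2 at both follow-ups), power was 0.72–0.73 without the covariate and 0.71–0.73 with it, so there is no gain.

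**4. A contrast at one follow-up.**
- Unadjusted variance: 1.00 SD².
- Adjusted for baseline area: 1 − 0.5² = 0.75 SD².
- Share of variance due to sex: s = 0.25 D²/6.25, which is 0.04 at D = 1.0 and 0.25 at D = 2.5.
- Baseline plus sex: (1 − s) − (0.5 − s)²/(1 − s). At s = 0.04 this is 0.96 − 0.2116/0.96 = 0.74. At s = 0.25 it is 0.75 − 0.0625/0.75 = 0.67.
- Further cut in standard error: 1 − √(0.7396/0.75) = 0.7% to 1 − √(0.6667/0.75) = 5.7%.

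With 25 per arm the standard error is 2.5 × √(2/25) = 0.71 unadjusted, 0.61 with baseline (× √0.75), and 0.61–0.58 with baseline and sex. Power for the 1.0-point contrast is 0.28 unadjusted and 0.36 with baseline. If sex and body size together explain an assumed 10–40% of the variance, it becomes 0.37–0.44.

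**5. Chance imbalance in sex.** The SD of the difference in male share between two arms of 30 is √(2 × 0.25/30) = 0.129. Times D, this moves an unadjusted follow-up contrast by 0.13–0.32 cm² per SD of imbalance. With baseline area in the model (slope 0.5), half remains: about 0.06–0.16 cm².

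**The case against.** **The interaction is unaffected.** The mixed ANOVA also tests group by time, and stable sex or body-size differences drop out of that test. This stands. A reader might infer that explainable variation inflates the error of every planned test, but step 3 shows that it does not.

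**Most of the gain is baseline area, not sex.** This also stands. Compared with no adjustment at all, sex would cut the standard error by 1 − √0.96 = 2% to 1 − √0.75 = 13%. Once baseline is in the model, 0.7–6% is left. The sex difference behind these figures is an assumption.

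**No bias.** Correct. Chance imbalance is already covered by the standard error, so it is not a second harm on top of lost precision. Nothing in the article supports reading the planned comparison as invalid.

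**The tests need not be pure false alarm.** The demographic variables are recorded after allocation and the physiotherapists are not blinded. A difference could therefore reflect a fault in allocation or recording. The chance-only statement holds under intact randomisation; significance tests are a poor way to find such faults.

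**Nobody says the tests will drive adjustment.** True. The article attaches no consequence to them, so data-driven adjustment is a risk left open and not a stated plan.

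**Covariates belong in an analysis plan that is not shown.** A bare omission would be excused on this ground. Here the article positively fixes both the baseline tests and a model whose effects are time, group and their interaction, with baseline as a response. That is a stated choice open to comment.

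**Conclusion.** The point holds in limited form. The baseline P values tell the reader nothing useful under intact randomisation, with up to a 37% chance of at least one false alarm for the listed variables, or 51% with the outcome scores, if independent.

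The model forgoes precision in the group main effect, which is the test behind N = 75, and in any between-group comparison at a single time point, including the rank-test fallback. The larger part of the loss rests on the article's own correlation of 0.5: a variance of 1.00 against 0.75 SD². The smaller part rests on an assumed sex difference: 0.75 against 0.74–0.67 SD². The article gives no figure for how much sex or body size explains.

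The documents do not support a claim of bias, or of lost precision in the group-by-time interaction. This is an inexpensive improvement that should be made; it does not undermine the trial.

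**What to change.** 1. Delete the baseline significance tests and present baseline characteristics by arm descriptively.
2. Replace the mixed ANOVA that treats baseline as a response level with a prespecified ANCOVA, or a longitudinal model of the 8-week and 3-month values. Use the outcome's own baseline as covariate for every outcome.
3. For muscle area, add sex and one named body-size measure, BMI. Use the same covariates for every arm contrast.
4. Report the model with baseline alone as a sensitivity analysis.
5. State what replaces the rank-test fallback, since it cannot carry covariates; the same model with bootstrap intervals is one option.

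**Cost.** No new data, about three degrees of freedom (baseline, sex, BMI), and a documented change of the stated model. The change must be fixed before arms are compared. Trial status expected follow-up to end by September 30, 2021, so the amendment should be dated. If outcomes have already been compared by arm, the adjusted analysis should be labelled as decided afterwards.
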